### Outcomes assessments

Measures will be assessed at baseline, 13 weeks and 26 weeks.

Primary outcome measures will be blood glucose management (HbA_1c_), weight and mood. Secondary outcome measures include level of exercise, confidence to manage diabetes (self-report) and psychosocial well-being (self-report) using validated tools. The research assistant collecting the data will be uninformed of group allocation.

### Measures

Details about participants, including age, sex, height, education level, employment status and current medications will be obtained at baseline. Weight, waist girth and HbA_1c_, will be measured at each time point (baseline and 13 and 26 weeks). Participants will undergo a blood test at each time point, at Monash Medical Centre, Melbourne, Australia. Normal HbA_1c_ will be assayed on site at Southern Cross Pathology, Monash Medical Centre, Melbourne, Victoria, Australia. Assay instrument is Adams A1C HA-8160 automatic Glycohaemoglobin analyzer. The method is based upon the principles of high performance liquid chromatography (HPLC).

The following validated self-report measures will also be measured at each time point:

•**
*Mood:*
** The Depression, Anxiety and Stress Scale (DASS) [35] is a 21-item scale that assesses three negative emotional states: Depression, Anxiety and Stress and is shown to have excellent psychometric properties in adults [36].

•**
*Experience of demoralisation:*
** The Demoralisation Scale [37] is a 24-item self-report scale with a Cronbach’s alpha of 0.96, measuring depression commonly seen in the physically ill – particularly aspects of helplessness, hopelessness and loss of meaning [37,38].

•**
*Social support:*
** The Multidimensional Scale of Perceived Social Support Scale [39] is a 12-item scale that measures perceived social support from family, friends and significant others. This scale has proven to be psychometrically sound in diverse samples with strong test-retest reliability over a 2–3 month interval (*r* = 0.72 to 0.85), and internal consistencies of the total scale and sub-scales which are high (Cronbach’s Alpha = 0.79 to 0.98) [39].

•**
*Self-efficacy:*
** Diabetes Empowerment Scale – Short Form [40] is an 8-item self-report scale which is a valid and reliable measure of perceived ability to manage the psychological and social demands and challenges associated with diabetes [40]. Higher mean scores indicate greater level of confidence managing one’s diabetes.

•**
*Level of exercise:*
** Participants will be asked to record the total number of steps taken over any three days within a seven day period. This will be measured using a Be Active pedometer (Multifunction Pedometer, WWA2026, Reed Switch Technology) provided to them at the initial assessment. A three day period was noted by Tudor-Locke et al. [41] as a sufficient number of days to reliably measure physical activity in adults.

•**
*Quality of Life:*
** The EuroQol (EQ-5 D) [42] is a brief self-report measure of subjective quality of life. This measure has been used in intervention studies with depressed patients [43], and will allow the calculation of quality-adjusted life years (QALY).

**
*The Working Alliance Inventory – Short Form, Participant/Therapist Version*
** (WAI) is a valid measure of treatment alliance [44] and will be completed by participants in the intervention group following phone sessions at 1, 3 and 6 weeks, and by the Health Coach at these times.

### Study integrity and quality assurance

Ethical approval for this study has been obtained from both the Monash Health Human Research Ethics Committee and the Monash University Human Research Ethics Committee. The study design will be guided by the CONSORT statement [45,46]. Each participant will be screened for eligibility and enrolled if eligible and consenting. To ensure consistency and best practice, participant’s height, weight and girth measurements are taken as per recommendations outlined by the World Health Organization [47]. The randomisation process will be conducted by an independent statistician. Assessments at baseline, 13 and 26 weeks will be carried out by a research assistant who will be uninformed of group membership. All Health Coaches who will be delivering the intervention are qualified Diabetes Educators and trained in the Whole Person Model. As well as the initial training, reflective practice support and supervision will be provided to the Health Coaches. The Project Coordinator will monitor the delivery of the intervention via recordings of phone sessions for the first participant of each Health Coach and random subsequent coaching sessions. Constructive feedback will be provided where necessary, and a fidelity checklist completed. Quality of health coaching will also be assured using measures of treatment alliance. No significant risks to participants are anticipated.

### Sample size justification

Using information from comparative studies, 150 participants are required to detect a between group difference of 0.7% (SD ± 1.5) in HbA_1c_, with 80% power and at an alpha level of 0.05 [48]. Similarly, 150 participants are needed to detect a between group difference in weight of 4.4 kg (SD ± 9.6) with 80% power and at an alpha level of 0.05 [49]. Based on a comparative sample using the DASS [50], at least 116 participants are required to detect a hypothesised reduction of 25% in DASS score (20 to 15, SD ± 9.6). On the basis of this analysis, and assuming a dropout rate of 20% based on prior experience, we estimate that a recruited sample of 180 will be required and be sufficient to give the requisite power.

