**Methods/Design:**

In a parallel-group randomised trial, 180 people with type 2 diabetes of between 2–10 years duration will be recruited via invitation through the Australian National Diabetes Services Scheme. Participants will undergo baseline assessment, followed by randomisation to either intervention or control condition. Control participants will receive fact sheets containing key information about diabetes self-management. The intervention group will receive the INSPIRED (Individual Support & Resources for Diabetes) Manual and be assigned a Health Coach. The INSPIRED Manual consists of six modules that provide key information about diabetes and disease management using the Whole Person Model. Engagement is facilitated by interactive tasks and contact with a Health Coach over seven weeks – an introductory face-to-face session, and six subsequent contacts by phone following each module. Follow-up assessments occur at 13 weeks (post-intervention) and 26 weeks. Primary outcomes include blood glucose management (HbA_1c_), weight and mood. Secondary outcomes include level of exercise, confidence to manage diabetes, and psychosocial well-being.

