### Randomisation

The randomisation process will be conducted by an independent statistician. Stata Version 12 [34] statistical package will be used for the random allocation of subjects to either the intervention or the control group. To ensure equal allocation (1:1), block randomisation method will be used. A pre-defined randomised list containing ID numbers and their respective treatment allocation will be provided to the Project Coordinator (DP) who will not be involved in taking measurements, data management or statistical analyses. ID numbers will be assigned to participants in consecutive order to avoid selection bias.

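### Recruiting 180 with 20% dropout leaves 144 completers, not the 150 the plan requires; 150 completers need 188 recruits

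*Protocol article*

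**What the plan says.** The section Sample size justification sets three requirements, one for each primary outcome:

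- HbA1c: "150 participants are required to detect a between group difference of 0.7% (SD ± 1.5" percentage points).
- Weight: "150 participants are needed to detect a between group difference in weight of 4.4 kg (SD ± 9.6" kg).
- Mood: "at least 116 participants are required to detect a hypothesised reduction of 25% in DASS score (20 to 15, SD ± 9.6").

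For HbA1c and weight the conditions are given as "with 80% power and at an alpha level of 0.05". The section then moves to the recruitment target: "assuming a dropout rate of 20% based on prior experience, we estimate that a recruited sample of 180 will be required and be sufficient" for the power sought. The abstract (Methods/Design) repeats the target as "180 people with type 2 diabetes". The Randomisation section fixes the allocation: "To ensure equal allocation (1:1), block randomisation method will be used". No inflation formula is shown, and nothing elsewhere in the article alters the 150, the 20% or the 180.

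**The concern.** An allowance for dropout has to leave the required number after the losses. If a fraction d is lost, the number to recruit is N/(1 − d). Multiplying by (1 + d) always gives too few, because the loss applies to the recruited number and not to the required one. The stated 180 is exactly what that multiplication gives for 150 and 20%.

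The statement at stake is that 180 is enough for the required power. Weight is the outcome most exposed: its requirement is the full 150, with no rounding margin, and it is a primary outcome.

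**Working it through.** **Inputs, all from the protocol article.** From Sample size justification: HbA1c difference 0.7, SD 1.5; weight difference 4.4 kg, SD 9.6; DASS difference 20 − 15 = 5, SD 9.6; power 80%, alpha 0.05; dropout 20%; recruited 180. From Randomisation: 1:1 allocation. Sidedness is not stated. Two-sided is assumed here, and step 1 supports it. Power and alpha are not repeated for the DASS, so the same values are assumed.

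**Step 1: reproduce the base sample sizes.** By the normal approximation, n per arm = 2 (1.960 + 0.842)² (SD/difference)² = 15.70 × (SD/difference)².

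| Outcome | (SD/difference)² | n per arm | Total | Total by t-test | Plan |
|---|---|---|---|---|---|
| HbA1c | (1.5/0.7)² = 4.592 | 72.1 → 73 | 146 | 148 | 150 |
| Weight | (9.6/4.4)² = 4.760 | 74.7 → 75 | 150 | 152 | 150 |
| DASS | (9.6/5)² = 3.686 | 57.9 → 58 | 116 | 118 | 116 |

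Weight and DASS match exactly, and HbA1c matches apart from a small upward rounding. One-sided totals would be 114, 118 and 92, which do not match. So 150 is the analysable number before any allowance for dropout, and it is sound.

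**Step 2: the dropout allowance.**

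- Needed: 150/(1 − 0.20) = 187.5, so 188 (94 per arm). Check: 188 × 0.80 = 150.4.
- Stated: 180. Completers: 180 × 0.80 = 144, a shortfall of 150 − 144 = 6 completers, or 188 − 180 = 8 recruits.
- Likely origin: 150 × 1.20 = 180. This is inferred from the exact match.
- Dropout at which 180 would suffice: 1 − 150/180 = 16.7%.

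**Step 3: power with 144 completers (72 per arm).** By the normal approximation, power = Φ(difference/SD × √(n/2) − 1.960), and √(72/2) = 6.

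- Weight: 0.4583 × 6 = 2.750; Φ(0.790) = 78.5%.
- HbA1c: 0.4667 × 6 = 2.800; Φ(0.840) = 80.0% (79.96% unrounded).
- DASS: 0.5208 × 6 = 3.125; Φ(1.165) = 87.8%.

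Power at the required 150 is shown alongside, so that the effect of dropout can be separated from the choice of method:

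| Outcome | 150, normal | 144, normal | 150, t-test | 144, t-test |
|---|---|---|---|---|
| Weight | 80.1% | 78.5% | 79.6% | 78.0% |
| HbA1c | 81.5% | 80.0% | 81.0% | 79.4% |
| DASS | 89.1% | 87.8% | 88.7% | 87.4% |

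Within either method the missing six completers cost about 1.6 points for weight and for HbA1c, and 1.3 for the DASS. The further half point or so between the two methods has nothing to do with dropout.

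**The case against.** The strongest reply is that little follows from the slip.

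- **Size.** By the method that reproduces the plan's own numbers, HbA1c still has 80.0% and the DASS is well above 80%. Only weight falls short, by about 1.5 points. This stands and limits the weight of the point. It does not rescue the sentence, because weight is a primary outcome and the article itself states 150 for it.
- **The 20% is a planning guess.** At 16.7% dropout, 180 gives exactly 150. True, but the plan assumes 20%, and the allowance has to match the rate it names.
- **The origin is inferred.** The article never writes 150 × 1.20. This stands too, but the shortfall does not depend on how 180 was reached.
- **Intention-to-treat and imputation.** Statistical analyses plans intention-to-treat analysis but offers chained-equation imputation only as a possible sensitivity analysis. Imputation does not in general restore the information in outcomes that were never measured, and the sample size section itself treats dropout as a loss to be made good.
- **Covariate adjustment.** Adjusting for the baseline value could recover the loss. If it multiplies the residual variance by 1 − r², the weight requirement of 2 × 74.7 = 149.5 falls to 144 when 1 − r² = 144/149.5 = 0.963, that is r of about 0.19. But the article gives no correlation, does not name baseline values among its covariates, and does not base its calculation on adjustment.

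**Conclusion.** The concern holds. On the article's own inputs, 180 recruits with 20% dropout give 144 completers, which is six fewer than the 150 stated for HbA1c and for weight; 188 recruits are needed. The headcount error is plain arithmetic and rests on no assumption.

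The power consequence assumes a two-sided 0.05 test, 1:1 allocation, equal dropout in the two arms and an unadjusted comparison of means. On that basis weight has 78.0% to 78.5% power, HbA1c 79.4% to 80.0% and the DASS 87.4% to 87.8%, the lower figure in each pair being the t-test. The claim that 180 suffices is therefore wrong for weight, borderline for HbA1c and right for the DASS. The base sizes of 150 and 116 need no change. The loss is modest and does not threaten the design, but the sentence is wrong as written and easily put right.

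**What to change.** Correct the closing sentence of Sample size justification in one of two ways.

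1. **Keep 180.** State that with 20% dropout 144 completers are expected (72 per arm), giving about 78.5% power for weight, 80.0% for HbA1c and 87.8% for the DASS by the normal approximation (78.0%, 79.4% and 87.4% by the t-test), two-sided 0.05. Name the method. The cost is one sentence and a slightly less favourable power statement; no extra participants are needed.
2. **Keep 150 completers.** Change the recruitment target to 188 here and in the abstract. The cost is eight more recruits.

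If the team believes that dropout will be 16.7% or less, 180 can also stand, provided that rate replaces the 20% and is justified. Any appeal to a gain from baseline adjustment should state the correlation assumed and show a range.

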### Statistical analyses

Continuous variables will be assessed for their distribution and outliers prior to analyses. Variables will be transformed if distributional/linearity assumptions are violated. We will compare group characteristics using student t-test for continuous variables, Chi-square (χ^2^) or Fisher’s exact test for categorical variables. We will conduct univariable and multivariable linear regression analyses adjusting for appropriate covariates and test for interactions. For dichotomous outcomes, logistic regression analyses will be implemented. All analyses are to be conducted on an intention-to-treat basis (ITT). However, we may conduct a sensitivity analysis using the imputation method chained equations (ICE) if we find a disproportionate level of missing values that are assessed as missing at random (MAR). Stata Version 12 [34] will be used for all statistical analyses.

## Discussion

This study will examine the efficacy of a novel model of disease self-management. The novelty is the Whole Person Model, which integrates usual self-management principles with attention to the feelings of the person in a way that does not pathologize depression or anxiety, but seeks to understand it in the context of a person struggling, perhaps, with their disease and management of it. In this program we include access to a trained Health Coach as we have concluded from our experience that this offers necessary support to the person whilst they take in new information, and attempt significant and sometimes difficult, behaviour change. We know that both the integrated model and the support of the Health Coach are critical factors in this change. Such knowledge has informed the design of the study that compares the active intervention with a fairly passive approach of delivery of information in the control group. If shown to be effective, this model will be easily implementable in clinical practice. Diabetes Educators are commonly employed around the world, and the Whole Person Model is operationalized in the INSPIRED Manual. Consequently, the model could easily be widely implemented in a way that would have a huge effect on population health.

## Abbreviations

INSPIRED: Individual support & resources for diabetes; DAWN: Diabetes attitudes wishes and needs; CBT: Cognitive behavioral therapy.
